### Randomisation and treatment allocation concealment

A block randomisation method will be used to randomise subjects into groups that result in equal sample sizes. This method will ensure a balance in sample size across both groups over time. Blocks are small and balanced with pre-determined group assignments, which keeps the numbers of subjects in each group similar at all times, whilst ensuring there is a 50:50 likelihood of participants being allocated to either group. Due to the possible influence of gender on the efficacy of strengthening exercise [32, 33], the study will only recruit male participants. After patient eligibility has been confirmed and informed consent obtained, a sealed envelope will be opened to reveal group allocation by an independent administrator not involved in the recruitment, treatment or assessment of study outcomes. A plain language statement will inform participants that they have an equal chance of receiving the residential MDT or individualised outpatient intervention. Group allocation will be documented and communicated to the supervising therapists by the independent administrator. Prior to the study, all treating staff will have received a briefing on the study protocol, the ethical, clinical and scientific basis of the study, the randomisation process and specific intervention for each treatment group, in line with the study protocol. It is not possible, relevant or necessary to blind participants to treatment allocation in this study. The clinical staff supervising both groups will be, by necessity, unblinded. Day and Altman [34] suggest blinding assessment by using non-involved assessors to record outcome scores. This is not possible in our study as independent assessors with specific knowledge of quantification of clinical outcomes are not available due to specialist staff man-power limitations. To minimise the potential influence of outcome assessors, instructions are standardised to ensure consistency in measurement. A medical statistician assisting with statistical analysis will be blind to group allocation until completion of the analysis.

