**Methods/design:**

The trial will be conducted at the Defence Medical Rehabilitation Centre, Headley Court, UK. One hundred military male participants with clinical indicators of non-arthritic intra-articular hip pain will be randomly allocated to either: (1) 7-day residential multidisciplinary team intervention, *n* = 50; (2) 6-week physiotherapist-led outpatient intervention (conventional care), *n* = 50. Measurements will be taken at baseline, post-treatment (1-week MDT group; 6-weeks physiotherapy group), and 12-weeks. The primary outcome measures are the function in daily living sub-scale of the Copenhagen Hip and Groin Outcome Score (HAGOS), the physical function subscale of the Non-arthritic Hip Score (NAHS), and VAS pain scale. Secondary outcomes include objective measures of physical capacity and general health. An intention-to-treat analysis will be performed using linear and mixed models.

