### Design

The study is a superiority parallel-group, randomised controlled trial (RCT) of a 7-day residential, multidisciplinary intervention (MTD programme), and individualised physiotherapy outpatient care (IP programme) with 3-month follow-up. Measurements will be taken at baseline, post-treatment (7-day MDT; 6-weeks IP) and 12-weeks. We considered including a sham control treatment group but felt in a well-motivated young military cohort this could have a negative impact on recruitment. Trial participants, assessors and clinical/research staff will be un-blinded to treatment allocation. The protocol will conform to the CONSORT (Consolidation of Standards of Reporting Trials) guidelines for non-pharmacological interventions [25], and principles of the Declaration of Helsinki [26].

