### Procedure

The procedure and flow of participants is outlined in Fig. 1. Patients with symptoms of hip pain will undergo preliminary screening conducted by their local unit medical officer. The only screening criteria used at this initial stage is the patient reporting symptoms of hip/groin pain for at least 3-months. Potential participants will then attend a multidisciplinary injury assessment clinic (MIAC) at DMRC for a comprehensive musculoskeletal examination by a specialist rehabilitation consultant, and experienced musculoskeletal physiotherapist. The purpose of the MIAC is to establish the patient’s eligibility for inclusion in the study. Because attendance at the MIAC is directly linked to this study, patient consent to attend the MIAC will be sought in advance via postal consent forms and a patient information sheet, and follow-up telephone calls from study administrators where necessary. The information sheet will detail the nature of the study and will include confirmation that consenting eligible participants will be randomly assigned to one of the following two treatment groups:

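### Small balanced blocks at a single open-label centre leave later allocations partly inferable, a risk of selection bias that undisclosed, randomly varying block sizes would reduce

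*Protocol article*

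**What the plan says.** The randomisation section of the protocol article describes the blocks in these terms: "Blocks are small and balanced with pre-determined group assignments, which keeps the numbers of subjects in each group similar at all times". It adds that the method works while "ensuring there is a 50:50 likelihood of participants being allocated to either group".

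The abstract places the whole trial at one centre: "The trial will be conducted at the Defence Medical Rehabilitation Centre, Headley Court, UK". No stratification is described, so there appears to be one allocation sequence.

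On knowledge of allocation, the Design section says: "Trial participants, assessors and clinical/research staff will be un-blinded to treatment allocation". The randomisation section says: "Group allocation will be documented and communicated to the supervising therapists by the independent administrator". Treating staff are also briefed beforehand on "the randomisation process and specific intervention for each treatment group". The Procedure section has a member of the clinical team tell patients which group they are in.

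On entry to the trial, the Procedure section says: "Potential participants will then attend a multidisciplinary injury assessment clinic (MIAC) at DMRC for a comprehensive musculoskeletal examination by a specialist rehabilitation consultant", together with an experienced physiotherapist. The purpose of that clinic is to establish eligibility.

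The safeguard is that, once eligibility and consent are settled, "a sealed envelope will be opened to reveal group allocation by an independent administrator", and this administrator takes no part in recruitment, treatment or outcome assessment.

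**The concern.** A balanced block limits how far the two arms can drift apart, and the smaller the block, the tighter the limit. That limit is also what gives the next assignment away: when one arm is ahead, the other is more likely to come next, and near the end of a block the next assignment can be certain. An envelope protects its own contents, but it does not protect against inference from envelopes already opened.

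The conditions for such inference are present here. There is one sequence and one centre. The arms are plainly different to anyone working there (a residential week against outpatient visits over six weeks), and staff are unblinded. Several entry criteria in Table 1 leave room for judgement, such as whether a co-morbidity precludes safe participation or whether the patient has enough time for appointments. Someone with a view on which patients suit residential care could, even without intending to, let an expected assignment influence who is judged eligible or invited, and when. The groups could then differ in prognosis at entry, including in ways that are not measured.

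**Working it through.** The article states no figure for predictability, so there is none to reproduce. Its 50:50 statement is right for a participant before any history is known. The question is how far it holds once earlier assignments in the block are known.

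**Inputs.** The allocation is 1:1 in balanced blocks (randomisation section). There is one centre and no described stratification. Planned recruitment is 100 (Sample size section). Block size is not given, so sizes 2, 4 and 6 are assumed, with 8 and 10 for comparison.

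**Case 1: size fixed and known.** Write the block size as b = 2k.

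*Certain assignments.* An assignment is certain once one arm has used all its k places. The expected share is 1/(k + 1). For b = 4 this can be counted directly: of the six possible orders, AABB and BBAA fix their last two places and the other four fix only the last. That gives (2×2 + 4×1)/6 = 1.333 of 4, or 33.3%.

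*Correct guesses.* Always guess the arm with more places left. For b = 4 the chances of being right at positions 1 to 4 are 1/2, 2/3, 2/3 and 1. The sum is 2.833, and 2.833/4 = 70.8%. In general the expected number correct per block is k + ½[4^k / C(2k, k) − 1]. For b = 2 this gives 1 + ½(4/2 − 1) = 1.5 of 2. For b = 6 it gives 3 + ½(64/20 − 1) = 4.1 of 6.

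| Block size | Known with certainty | Guessed correctly |
|---|---|---|
| 2 | 50.0% | 75.0% |
| 4 | 33.3% | 70.8% |
| 6 | 25.0% | 68.3% |
| 8 | 20.0% | 66.6% |
| 10 | 16.7% | 65.3% |
| Unpredictable allocation | 0% | 50% |

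With 100 participants the percentages are also counts: with blocks of 4, about 33 assignments would be certain and about 71 guessable.

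**Case 2: sizes 4, 6 and 8 in random order.** Sequences of 100 were simulated.
- Certain assignments, for an observer who knows the set of sizes but not their order: about 2%.
- Correct guesses, always naming the arm that is behind: about 68%.

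Varying the size therefore removes nearly all the certainty but little of the guessability, because the running imbalance still points to the arm that is behind.

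**Cost in balance.** If recruitment stops inside a block of 8, the arms differ by at most 4, that is 52 against 48. The variance of a difference in means relative to 50 against 50 is (1/52 + 1/48)/(1/50 + 1/50) = 0.04006/0.04 = 1.0016, an increase of under 0.2%.

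**The case against.** The strongest reply is that the chain from block size to biased entry is not documented. Allocations are said to go to the supervising therapists. Nothing says that the consultant and physiotherapist at the assessment clinic are those therapists, or that anyone keeps an ordered list. A reader might infer that staff know every past allocation, but the text does not go that far: being unblinded is not the same as tracking the sequence. This stands. Overlap of staff is plausible at one centre, since the residential team also includes a consultant physician and a physiotherapist, but it remains an inference.

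Second, the certainty figures need a block size that is both fixed and known to staff. A journal article commonly leaves block sizes to the full protocol, so their absence is not a fault, and a briefing on the randomisation process need not disclose them. Blocks of 4, 6 and 8 in random order could even fit the article's wording. This also stands and makes the certainty figures conditional. The guess rates depend less on it: about 65% to 75% for fixed blocks of 2 to 10, and about 68% for the varying scheme.

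Third, the safeguards are real. The envelope is opened after eligibility and consent by someone outside the trial team, patients are randomised consecutively, and Table 1 lists explicit criteria. These narrow the room to act on a guess without closing it.

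Fourth, it is tempting to say that no analysis could later repair such a bias. That is too absolute: the plan presents baseline comparability and analyses change from baseline, which can reveal or partly address measured imbalance. Unmeasured imbalance would remain. Nor do the open-label, patient-reported outcomes strengthen this point, because they raise a different kind of bias.

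**Conclusion.** The point holds as a design risk. The article chooses small balanced blocks for the sake of constant near-equality, at a single centre with unblinded staff, and its concealment measures do not address inference from earlier allocations. If the size is fixed and known, 50%, 33% or 25% of assignments are certain with blocks of 2, 4 or 6, and 75%, 71% or 68% can be guessed, against 0% and 50% under unpredictable allocation. These figures assume one unstratified sequence and an observer who follows it.

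A reader might go further and conclude that concealment has failed or that selection bias will occur. The documents do not support that. They do not show recruiters tracking the sequence, and they do not give a block size. A weakness in the design is shown, but not a bias in the result. It is worth correcting because the remedy is cheap and near-equality at every moment gains the analysis almost nothing.

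**What to change.** 1. Use a computer-generated list of permuted blocks of randomly varying size, for example 4, 6 and 8 in random order.
2. Withhold the sizes from all recruiting, assessing and treating staff, and leave block details out of the pre-study briefing on the randomisation process.
3. In the randomisation section, replace the aim of small blocks and constant near-equality with approximate balance between the arms, and state that block sizes vary and are not disclosed.

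If the full protocol already does this, only the wording in step 3 and a check on the content of the briefing are needed.

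The gain should be described honestly: certain assignments fall to about 2%, while guesses from the running imbalance stay about 68% correct. The cost is a new list and a possible final imbalance of at most 4 participants. The planned mixed models do not need equal arms and tolerate this.

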### Interventions

The content and protocols for the study interventions are described in a MILO study intervention guide [see Additional file 1]. Table 2 provides a summary of the components of the MDT residential intervention. Table 3 provides an overview of the IP and MDT treatment schedules. Following the recommendations of Bennell et al. [29], a systematic approach to designing all aspects of the intervention has been adopted that ensures it is based on theory, evidence, reflects elements of best practice, and is reproducible and reportable. The MDT residential and IP outpatient group programmes in this study will employ a semi-structured protocol, which provides guidance on exercise prescription, but can be tailored to meet individual patient assessment findings and progression. Written guidelines for individual tailoring of activity and treatment prescription will be provided to supervising therapists. Designing a patient care plan that is individually tailored from a standardised menu of interventions ensures our methodology is consistent with the ‘ideal standard of clinical practice’ [35], and research designs of previous studies [5, 27, 29, 36, 37]. The IP outpatient intervention will be administered by a senior chartered physiotherapist. A broader MDT including specialist physician, physiotherapist, occupational therapist, exercise rehabilitation specialist and nutritionist at DMRC will deliver the residential programme. All treating therapists will attend a training session at DMRC which will focus on the exercise, manual therapy and education interventions to ensure a standardised approach to treatment across both interventions and therapy staff. Whilst the delivery of therapeutic interventions by several MDT staff risks an increase in treatment variation through the influence of therapist personality and style, it allows a more practical delivery mode that mimics clinical practice, and will enhance the generalisibility of study findings [5].

**Table 2 Tab2:** Multidisciplinary team (MDT) residential intervention – components of treatment

Treatment modality	Treatment content	Treatment goals	Frequency per week (duration)
Group exercise	Strengthening exercises, active range of motion exercises, functional balance drills, gait drills, progressive co-ordination drills, non-weight-bearing aerobic/endurance exercise, minor team games.	Restore strength of deep hip stabilisers, improve core strength, increase joint range of motion, improve balance and neuromotor control, improve muscle endurance, promote group cohesion and social support.	12 (30–45 min)
Individual physiotherapy^a^	Manual therapy techniques, muscle activation and timing patterns, active and passive range of motion exercises, advice on home-exercise, gait re-education training.	Improve quality and timing of movement, improve muscle strength, reduce pain, increase joint range of motion, induce relaxation, promote normal walking gait.	5 (30 min)
Hydrotherapy/swimming	Non weight-bearing aerobic exercise, strengthening exercises, active range of motion exercises, self-paced recreational swimming, progressive/assisted weight-bearing exercise and activity.	Improve muscle strength, improve aerobic capacity, increase joint range of motion, improve confidence in weight-bearing, induce relaxation, promote enjoyment and variety of treatment.	3 (60 min)
Individual occupational therapy^b^	Relaxation techniques, postural re-education, cognitive behavioural therapy (CBT) techniques, self-help coping strategies, pain management.	Induce relaxation, promote behavioural change, control pain, correct/improve poor posture.	3 (60 min)
Patient education	Coping with pain, benefits of exercise, joint protection, anatomy and pathology of hip pain, nutrition.	Activity modification, reduction of pain, promotes behavioural change, weight management, improve knowledge of treatment options, improve ability to relax, improve knowledge of self-help techniques.	2 (60 min)

^a^Exercise dosage, progression and intensity will be governed by the physiotherapist and tailored to the needs of each individual patient; ^b^Occupational therapy referrals will be individually prescribed to selected patients

**Table 3 Tab3:** Overview of Outpatient Individual Programme (IP Group) and Residential (MDT Group) Study Treatment Schedule

Outpatient (IP) Protocol	Residential (MDT) Programme
Session 1 (45–60 mins)^a^	Day 1
• Subjective and objective assessment (20–25 mins)	• Admission MDT clinic and baseline measures
• Patient education (5-mins)	Day 2
• 1–2 manual therapy techniques (5–10 mins)	• Group-based introduction to treatment goal 1
• Teach target exercise from treatment goals^c^ 1 and 2 (15–20 mins)	• Group-based introduction to treatment goal 2
• Confirm home-exercises (5-min)	• Individual therapy appointments in accordance with patient timetable (PT/OT)^b^
Session 2 (45–60 mins)	Day 3
• Subjective and objective re-assessment (10-mins)	• Group-based introduction to treatment goal 3
• Patient education (5-mins)	• Group-based introduction to treatment goal 4
• Manual therapy techniques (15–20 mins)	• Group-based education topic 1 (‘about hip pain’)
• Teach revised home exercises; check log-book (15–20 mins)	• Individual therapy appointments in accordance with patient timetable (PT/OT)
Sessions 3 to 8 (30–40 mins)	Day 4
• Subjective and objective re-assessment (5-mins)	• Group-based introduction to treatment goal 5
• Manual therapy techniques (15-mins)	• Consolidate individual patient exercise programme
• Patient education & advice (5-mins)	• Group-based education topic 2 (‘activity modification’)
• Progress home-exercises; check log-book; address adherence issues (15-mins)	• Individual therapy appointments in accordance with patient timetable (PT/OT)
	Day 5
	• Group-based exercise targeting individual patient priorities
	• Group-based education topic 3 (‘benefits of exercise’)
	• Individual therapy appointments in accordance with patient timetable (PT/OT)
	Day 6
	• Group-based exercise targeting individual patient priorities
	• Group-based education topic 4 (‘pain management’)
	• Individual therapy appointments in accordance with patient timetable (PT/OT)
	Day 7
	• Confirm individual home-based exercise programme; issue log book;
	• Discharge clinic with multi-disciplinary team
Follow-up period	Follow-up period
• 4 to 6 home exercises, 3-times per week	• 4 to 6 home exercises, 3-times per week

^a^Timing does not include baseline outcome measures; ^b^PT = Physiotherapist; OT = Occupational Therapist; ^c^ Explanation of treatment goals are contained in Additional file 1

The goals of treatment are the same for both the residential and outpatient groups. The specific programme design will differ to reflect the contrasting structure in each setting, and to accommodate the individual participant progression. The core components of treatment are as follows:

### Exercise therapy

It is beyond the scope of this study protocol paper to detail every individual exercise used in the study interventions. The exercise programme incorporates strengthening, flexibility/range of motion, and functional balance and neuromuscular control exercises in accordance with current evidence-based guidelines, and exercise recommendations for the conservative management of intra-articular hip disorders [1, 10, 13].

#### Muscle strengthening exercise

A key component of the exercise programme is local stabilisation of the hip joint by retraining and strengthening of the global hip musculature. We will implement a comprehensive strengthening programme to optimise neuromuscular control, strength and stability of the hip. This includes exercises targeting gluteus medius, gluteus maximus, iliopsoas, quadratus femoris, obturator internus, inferior and superior gemelli, adductor brevis and pectinius [38]. We will also include core strengthening based on studies of hip muscle activity during the performance of core exercises [39], and its recommendation in clinical guidelines for the management of non-arthritic hip pain [40]. We also include functional, weight-bearing hip muscle strengthening including some proprioception exercises to optimise neuromuscular control, stability and strength of the hip in patient specific (military) activities. The programme acknowledges the importance of the deep hip rotators and gluteal group. These muscles act as deep stabilisers to steady the femoral head in the acetabulum, and provide dynamic control of hip joint stability [41]. The focus of the strengthening programme is based on low load exercise, commencing in non-weight bearing positions, 4-point kneeling, and progressing to fully weight-bearing functional positions promoting global muscle recruitment [1, 5]. Three sets of 8–12 repetitions are completed for each exercise. Graduated exercise progression is determined by the supervising therapist based upon participant feedback, re-assessment and individual response to training.

It should be noted that despite an abundance of information on the implementation of strength and conditioning principles with healthy participants, investigation regarding the application of these principles in rehabilitation programmes is lacking [42]. The dosage for strengthening exercises in this protocol aims to meet the ongoing challenge of designing treatment programmes that facilitate neurological and muscular adaptations whilst concurrently accommodating biological healing, recovery and the safety of the patient. The justification for the initial dosage of 3 × 8-12 repetitions takes account of the evidence suggesting pain provoked by exercise has been shown to reduce adherence to exercise in rehabilitation programmes [43, 44]. The study intervention programmes aim to stabilise pain within a given range-of-motion during the early stages of rehabilitation. Therefore a relatively conservative initial dosage is chosen that should allow a short period of adaptation whilst controlling for pain, thereby promoting exercise adherence. This repetition range has been recommended and used for strength exercise prescription in recent RCT protocols/studies for non-arthritic hip pain [5, 30, 45] and hip OA [27, 37, 46]. None provided references to sources of experimental evidence supporting selection of this exercise dosage, however, in two studies [27, 30] improvements in pain and function were reported following this programme.

